### Analyses

#### The effectiveness study

Data will be analysed according to the intention-to-treat (ITT) principle, accounting for all included participants regardless of whether or not they have responded to the follow-up assessments. Missing data will be handled using the Missing Value Analysis routine in the SPSS software (IBM SPSS Statistics 23, IBM Corporation, NY, USA).

Data analyses will consist of comparing outcome measurements at baseline (t0) and subsequent follow-up (t1, t2, and t3) assessments, with regards to within-group and between-group comparisons.

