### Assessment

The assessments for this study will consist of a baseline measurement (t0), which will take place before randomization, and three follow-up measurements after six (t1), 12 (t2), and 24 months (t3). Participants will be invited to each assessment by e-mail, and if necessary up to three reminders will be sent at five, ten, and 15 days after the first invitation, respectively. All assessments will be in the form of an online survey distributed via the survey data collection tool Easyresearch (QuestBack, Norway). In order to increase the response rate, participants will be offered an incentive of one cinema gift certificate, corresponding to approximately 11 Euros, for each assessment. The resulting survey contains 216 questions and takes approximately 30 min to complete.

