### Sample size

The sample size calculation is based on the ability to detect a medium or larger effect size, corresponding to a standardized mean difference (Cohen’s d) of > 0.05 [61]. Based on differences between means, an *a priori* calculation of the estimated sample size, using the G*Power software [62], and accounting for an unequal allocation ratio of 1.8 in favour of the intervention group, reveals that 140 participants need to be included in the trial, 90 in the intervention group and 50 in the control group (power = 0.80, α = 0.05, 2-tailed).

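### If the named SPSS routine is used to fill in missing follow-up values once, the planned comparisons have either understated standard errors or a diluted effect; the plan names no method that avoids both.

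*Protocol article*

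**What the plan says.** The relevant text is in the protocol article under Analyses, The effectiveness study. The analysis follows intention to treat, "accounting for all included participants regardless of whether or not they have responded to the follow-up assessments". On missing values it says: "Missing data will be handled using the Missing Value Analysis routine in the SPSS software" (version 23). The outcomes at baseline and at 6, 12 and 24 months are then to be compared "with regards to within-group and between-group comparisons".

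The section does not say which option of the routine is used, whether values are filled in once or several times, whether treatment arm enters the model, or how uncertainty about missing values reaches the standard errors. No attrition rate appears anywhere in the article. The Assessment section describes e-mailed online surveys of 216 questions, with up to three reminders and a gift certificate per assessment to raise response.

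**The concern.** The plan fixes two things together: non-responders count in the analysis, and one software routine deals with their missing values. What follows is described only as comparisons between time points and between groups. A plausible implementation is therefore to have the routine write one completed dataset, by EM or regression, and to run ordinary tests on it. Those tests cannot tell a filled-in value from an observed one.

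What is at stake depends on the imputation model. If arm is in it, the filled-in values repeat the estimated arm difference without adding information, and the reported precision is too high. If arm is not in it, the filled-in values carry no arm difference, and a real effect is diluted. The three follow-ups run to 24 months and depend on survey response, so missing values are likely to be more than a handful.

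**Working it through.** **The plan's own figure.** The Sample size section gives "140 participants need to be included in the trial, 90 in the intervention group and 50 in the control group" ("power = 0.80, α = 0.05, 2-tailed", allocation ratio 1.8). With d = 0.5, the control arm needs (1 + 1/1.8) × (1.960 + 0.842)² / 0.5² = 48.8, so 49 and 89, total 138. The exact noncentral-t calculation gives 50 + 90 = 140, power 0.804. The figure is reproduced, and only with d = 0.5; the printed "corresponding to a standardized mean difference (Cohen’s d) of > 0.05" would need about 13,676 participants and is a separate matter. So 140 is the complete-data requirement with nothing added for attrition.

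**Inputs.** From the article: 90 and 50 participants, two-sided α = 0.05. Assumed: a fraction m missing completely at random, m = 10 to 40%; correlation 0.5 between baseline and follow-up; one follow-up wave; one regression fill without added noise; 140 analysed as complete.

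**Case A, arm and baseline in the imputation model, baseline-adjusted test.** Filled-in points lie exactly on the fitted surface, so the estimate equals the one from responders alone.
- The residual variance is divided by the full sample and shrinks by about (1 − m).
- The design also counts the full sample, which shrinks the variance by another (1 − m).
- Reported SE / true SE is therefore about 1 − m, whatever the baseline correlation.
- Type I error is about 2Φ(−1.96(1 − m)). At m = 0.3: 2Φ(−1.372) = 17.0%.

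**Case B, arm omitted.** Filled-in values have no arm difference given baseline.
- The estimate is about (1 − m) × 0.50.
- Under the null, its true and its reported SE both shrink by √(1 − m), so the between-group error stays near 5%.
- With a real effect, the interval is centred in the wrong place. The complete-data SE is √0.75 × √(1/90 + 1/50) = 0.153. At m = 0.3 the SE is 0.153 × √0.7 = 0.128 and the bias is 0.15, or 1.17 SE. Coverage is Φ(1.96 − 1.17) − Φ(−1.96 − 1.17), about 78%.

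| Missing | 10% | 20% | 30% | 40% |
|---|---|---|---|---|
| A: SE ratio, formula | 0.90 | 0.80 | 0.70 | 0.60 |
| A: SE ratio, simulated | 0.90 | 0.78 | 0.69 | 0.60 |
| A: type I error, formula | 7.8% | 11.7% | 17.0% | 24.0% |
| A: type I error, simulated, adjusted | 7.2% | 12.7% | 16.7% | 23.7% |
| A: type I error, simulated, t-test | 8.1% | 10.2% | 13.3% | 17.4% |
| A: random residuals added, adjusted | 7.0% | 10.8% | 14.3% | 17.2% |
| B: type I error, simulated, adjusted | 4.5% | 5.2% | 5.7% | 5.3% |
| B: mean estimate of a true 0.50 | 0.45 | 0.40 | 0.35 | 0.30 |
| B: coverage of the 95% interval, formula | 94% | 89% | 78% | 61% |
| B: within-group change, intervention arm, type I error | 5.9% | 8.2% | 10.2% | 13.8% |
| Responders only, adjusted, type I error | 4.7% | 5.3% | 4.6% | 5.4% |
| Multiple imputation with arm (20 imputations), type I error | 5.2% | 4.9% | 4.4% | 4.2% |

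Formula and simulation agree to about one percentage point in Case A. The same within-group test in responders alone stays at about 5%.

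**The case against.** The strongest reply is that the article names a routine, not a method. A reader might infer that the plan says non-responders will be filled in once and analysed as if observed. It does not: the phrase about accounting for all included participants describes the analysis population, and how the routine's output would be used is not stated. That stands, and it makes the point conditional.

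A reader might also infer that false positives are inflated in every comparison, or that inflation and dilution of the between-group effect occur together. Neither holds. The two between-group harms are alternatives, depending on whether arm is in the imputation model, and the article does not say which would apply.

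The size is also open to challenge. The attrition rates are assumed; at 10% missing the harm is modest, and reminders and incentives may keep losses low. The simulation uses a single follow-up. Where another wave is observed, it could predict the missing one better and reduce the understatement; this was not tested.

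Finally, a condensed article may leave imputation details to a fuller plan. That covers the number of imputations and the list of predictors. It does not fully answer the point, because the article does choose a tool and pairs it with analysis of all participants, without naming anything that carries imputation uncertainty into the tests.

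**Conclusion.** The concern holds in conditional form. If the routine is used to write one completed dataset that is then tested as complete, neither version of the imputation model gives valid inference when there is a real effect. With arm included, between-group type I error is about 7, 12, 17 and 24% at 10, 20, 30 and 40% missing. With arm omitted, that error stays near 5%, but a true 0.50 shrinks in proportion to the missing fraction, interval coverage falls with it, and the planned within-group tests are inflated.

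These figures rest on data missing completely at random and one follow-up wave; all except the adjusted Case A ratio and the proportional shrinkage also rest on a baseline correlation of 0.5. With no attrition rate in the article, they show a range and do not predict this trial's error rate. The wording should be changed before analysis; it is not evidence that the results will be wrong.

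**What to change.** Under Analyses, The effectiveness study, replace the sentence on the SPSS routine with one of two methods:

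- a likelihood-based mixed model on all observed data from t0 to t3, with arm by time and baseline included, which uses the available data of every randomised participant without filling in values; or
- multiple imputation with arm, baseline and all waves in the imputation model, pooled by Rubin's rules.

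A sensitivity analysis for data not missing at random is a useful option, but the correction does not depend on it.

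The change needs no new data and no change of design. It costs slightly more analysis work and wider confidence intervals. The extra width reflects information that was never collected: for an unadjusted comparison of responders at d = 0.5, power falls from 0.804 to 0.761, 0.710, 0.651 and 0.583 at 10, 20, 30 and 40% missing. Filling in values once hides that loss without recovering it.

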### Allocation/Randomization

Participants will be randomly allocated to one of the two study groups after completing the baseline assessment. An unrestricted random allocation sequence will be generated by an external researcher using the Random Allocation Software [60]. Participants will be informed about their allocation by e-mail. Those participants who are randomized to the intervention group will receive further information about the study and about being assigned to a *Grubbel* group. The participants can choose between different dates for the group course, so they start on a day of their preference. Information about how to access the group course will be sent to the participants by e-mail. All participants will receive information about other support and information available according to care as usual (CAU), as described below.

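### The primary outcomes are all measured before randomisation, but neither the stated analysis nor the sample size mentions adjusting for the baseline score; stating that adjustment would improve precision at no cost in participants

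*Protocol article*

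**What the plan says.** The Assessment section sets a baseline survey before randomisation, with follow-up surveys at 6, 12 and 24 months. The Primary outcomes section lists CES-DC, Brief COPE, WHOQOL-BREF and AUDIT-C.

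On the analysis, the section on the effectiveness study describes comparisons: "Data analyses will consist of comparing outcome measurements at baseline (t0) and subsequent follow-up (t1, t2, and t3) assessments, with regards to within-group and between-group". It adds the intention-to-treat principle and a routine for missing data. It names no test, model or covariate.

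The Sample size section is "based on the ability to detect a medium or larger effect size". The calculation is described as "Based on differences between means", "accounting for an unequal allocation ratio of 1.8 in favour of the intervention group", with "power = 0.80, α = 0.05, 2-tailed". It arrives at 140 participants, 90 and 50, and uses no baseline correlation.

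On allocation: "An unrestricted random allocation sequence will be generated by an external researcher using the Random Allocation Software". No stratification is mentioned.

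**The concern.** The baseline score is usually among the best available predictors of the follow-up score on the same scale, and here it is collected for everyone before allocation. The analysis sentence treats t0 as something to be compared, and does not say that it will be adjusted for. Two natural readings of the sentence are less efficient than they need be. Comparing raw follow-up means ignores the t0 information. Comparing changes from t0 uses it with a fixed weight of one, which adds noise when the correlation is modest.

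The trial is sized at almost exactly 80% power for one test, with small, unequal arms and unrestricted allocation. Precision is therefore scarce, and some difference between the arms in baseline scores is to be expected. Leaving the choice open also allows raw, change-score and adjusted results to be compared before one is chosen.

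**Working it through.** **Inputs from the article.** Arms of 90 and 50; two-sided alpha 0.05; target power 0.80; a medium effect (Sample size). The t0 measurement precedes randomisation (Assessment). Allocation is unrestricted (Allocation/Randomization).

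**Assumptions.**
- d = 0.5. The printed threshold is 0.05, but that value would need about 13,700 participants (4,884 × 2.8 = 13,675), whereas 0.5 fits the word medium and reproduces 140.
- Correlation rho between t0 and follow-up of 0.3 to 0.7; the article gives none.
- Equal variance at t0 and follow-up, complete data, independent participants.

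**Step 1: reproduce the stated size.** The noncentrality for a two-sample t test is d × √(n₁n₂/(n₁+n₂)) = 0.5 × √(90 × 50/140) = 0.5 × 5.67 = 2.83, with 138 degrees of freedom. Power is 0.804. With 88 and 49 it is 0.795, so 140 is the smallest total that reaches 80% at this ratio. The stated figure is reproduced as an unadjusted comparison of two means.

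**Step 2: compare the possible analyses at the same 90 and 50.**
- Raw follow-up means: standardised effect d.
- Adjusted for t0 (ANCOVA): d/√(1 − rho²), 137 degrees of freedom.
- Change score: d/√(2(1 − rho)).

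At rho = 0.5 the adjusted effect is 0.5/√0.75 = 0.577, while the change-score effect is 0.5/√1 = 0.5, no better than the raw comparison.

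| rho | Raw follow-up | Change score | Adjusted for t0 | Gain over raw (points) | Gain over change score (points) |
|---|---|---|---|---|---|
| 0.3 | 0.804 | 0.662 | 0.839 | 3.5 | 17.7 |
| 0.4 | 0.804 | 0.729 | 0.867 | 6.3 | 13.8 |
| 0.5 | 0.804 | 0.804 | 0.902 | 9.8 | 9.8 |
| 0.6 | 0.804 | 0.882 | 0.940 | 13.7 | 5.8 |
| 0.7 | 0.804 | 0.953 | 0.976 | 17.3 | 2.3 |

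Gains are taken before rounding. Adjustment is ahead of both alternatives in every row. At rho = 0.5 it is worth as much as 140/(1 − 0.25) = 187 participants analysed without adjustment.

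**Step 3: chance baseline difference.** Its standard deviation, in SD units of the outcome, is √(1/90 + 1/50) = 0.176. A difference above 0.2 SD in either direction has a probability of about 26% for each outcome. Given an observed difference, a raw follow-up comparison is shifted by rho times that difference. At rho = 0.5 this is 0.5 × 0.176 = 0.09 SD for a one-standard-deviation imbalance, and 0.5 × 1.96 × 0.176 = 0.17 SD at the 95% limit. A change score is shifted by (rho − 1) times the difference, so at rho = 0.5 it errs equally in the opposite direction. Adjustment for t0 removes the expected shift.

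**Step 4: incomplete follow-up, for illustration.** If 20% of each arm were lost (an assumption), raw power would be 0.710 and adjusted power at rho = 0.5 would be 0.827.

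**The case against.** The strongest objection is that the article does not commit to an unadjusted analysis. A reader might infer from the analysis sentence that the primary comparison will be of unadjusted means. The text does not support that: it brings t0 into the analysis and names no model. Raw means, change scores and repeated measures all fit the wording. A repeated-measures model with a common baseline mean would already capture nearly all of the gain. A condensed article may also leave the model to an analysis plan that is not shown. This stands, and so the point is about what is not stated, not about a wrong method that has been fixed.

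The sample size does not settle it either. Sizing on two unadjusted means and then adjusting in the analysis is ordinary and conservative, and the calculation meets its own 80% target at d = 0.5. That also stands.

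The gain depends on an unknown correlation, which may be low for some outcomes. Follow-up runs to 24 months, internal consistency of the Brief COPE goes down to 0.58, and the exclusion of severe depression on the CES-DC narrows its baseline range. At rho = 0.3 the gain over raw means is only 3.5 points, and at 0.7 the gain over change scores is only 2.3.

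Finally, chance imbalance is not bias. The unadjusted randomised comparison is right on average, and its standard error already allows for such imbalance.

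What remains is that the sentence does describe what the analyses will consist of, gives the baseline score no role as a covariate, and leaves open two readings that are less efficient at every correlation considered.

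**Conclusion.** The point holds as a recommended improvement in efficiency. It does not show an invalid analysis or an underpowered design. No adjustment for t0 is stated for outcomes that are all measured before randomisation. Under the assumptions above, stating it gives power of 0.839 to 0.976, against 0.804 for raw means (a gain of 3.5 to about 17 points) and 0.662 to 0.953 for change scores. If change scores are what is meant, power falls below the 80% target whenever the correlation is under 0.5.

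Two stronger readings should be resisted. A loss of about 10 points is not established as a fact about this trial, since it holds only at an assumed correlation of 0.5. Nor will baseline imbalance bias the result: it affects precision, and the estimate conditional on the baseline difference that happens to occur. The shift of 0.17 SD belongs to the 95% limit and is not the typical case.

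**What to change.** In the effectiveness analysis, state that every between-group comparison of a primary outcome at t1, t2 and t3 is estimated with that outcome's own t0 score as a covariate. Use either ANCOVA at each time point, or one mixed model with arm, time, arm-by-time, t0 score and t0-by-time. Report the adjusted mean difference with its 95% CI as the effect estimate. Keep the sample size at 140, so that the gain serves as a reserve. If an analysis plan already says this, a sentence in agreement with it is enough.

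The cost is about one sentence. The t0 data are part of the planned assessments, SPSS fits these models, and ANCOVA spends one degree of freedom on the covariate. No participants or visits are added. The choice should be recorded before outcome data are compared by arm.

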#### The implementation study

The qualitative data will be analysed with thematic analysis in order to discover the main themes connected to the study aim and research questions.

## Discussion

This protocol describes the study of a Swedish version of the Dutch prevention program *Kopstoring*, called *Grubbel*, which is a web-based prevention program targeting 15–25-year-olds whose parents have substance use problems and/or mental illness. An addition to the original *Kopstoring* manual has been the inclusion of a more structured means of providing information relating to risky use of substances, addiction, and heredity. The effectiveness of *Grubbel* will be evaluated in a two-armed RCT, where the intervention group will be compared with CAU.

### Strengths and limitations

This study has a number of strengths. First, *Grubbel* is based on the Dutch *Kopstoring* program. *Kopstoring* is currently being evaluated in the Netherlands [42, 44], but results regarding the effects of the program have not yet been published. Nonetheless, this study will not only add to the evidence of the *Kopstoring* program, but also to web-based interventions in general and, in particular, to the relatively unexplored field of interventions targeted at adolescents whose parents have substance use problems and/or mental illness. Furthermore, there has been a request among Swedish professionals to develop a web-based intervention program for children and adolescents growing up in families with substance use problems, which increases the chance of widespread dissemination of the intervention if it proves to be effective. Finally, this study combines an RCT study, considered to be the strongest experimental design with regards to participant allocation bias, with a qualitative study of the intervention implementation.

There are also limitations to this study. One limitation concerns selection bias and thereby external validity, as recruitment requires either that individuals click on our Facebook ads to be considered for inclusion, or that they have been in contact with existing support. Thus, our sample may have certain personality traits, such as a help-seeking personality, possibly not seen in a broader audience. Furthermore, *Grubbel* is a relatively intense program and some individuals may not be included due to their inability to allocate 1.5 h per week to participate in the group chat. Among those who are included in the study, this may also pose a problem, and we may experience a lower degree of adherence.

### Implications for practice

Studies have revealed that the majority of children whose parents have substance use or mental health problems do not receiving existing support. In addition to problems with identifying individuals and recruiting them to available intervention programs, a related issue is how to make face-to-face intervention available in rural areas. This has been an issue raised among professionals working in the rural northern part of Sweden and a web-based solution has been requested. Thus, there is an urgent need to develop and evaluate novel intervention programs, such as web-based interventions, and disseminate successful programs to a broader audience. If this study demonstrates sufficient effectiveness in *Grubbel*, our aim is to implement and disseminate the intervention throughout Sweden, which will be a cost-effective means to provide support. This study therefore makes an important contribution, not only to this field of research but also to agencies, authorities, and organisations that provide support to this target group.
